### Randomization

A research coordinator will perform the randomization. A list of random numbers will be generated by an independent statistician. Eligible participants will be randomly assigned 1:1 to either the control group (fluid management based on the clinical information alone) or the treatment group (InBody S10 (InBody®, Seoul, Korea)-guided fluid management alone). Randomization will be stratified based on the institution and will utilize a randomized block design.

### Outcome measures

The primary outcome is to compare the rate of euvolemic status at 7 days from the CRRT start. The euvolemic status will be considered different when TBW/H^2^ between the day of CRRT initiation (D0) and 7 days from the day of CRRT initiation (D7) is less than − 2.1 or TBW/H^2^ at D7 is less than 13 L/m^2^. According to Rhee’s recent study, the group reaching TBW/H^2^ < 13 L/m^2^ had a significantly enhanced survival rate compared with that of the group that could not reach TBW/H^2^ < 13 L/m^2^ [17]. Moreover, our further study has revealed that the survival rate was significantly increased when the difference in TBW/H^2^ between CRRT initiation and at 7 days from CRRT start (TBW/H^2^
_at 7days_ – TBW/H^2^
_at CRRT initiation_) was less than − 2.1 L/m^2^, even though it was not sufficient to reach TBW/H^2^ < 13 L/m^2^ (data not shown). Therefore, we will also consider the euvolemia as TBW/H^2^
_at 7days_ – TBW/H^2^
_at CRRT initiation_ < − 2.1 L/m^2^ in this study. The secondary outcome is to investigate the 28-, 60-, and 90-day mortality rates in the control and treatment groups and to compare the mortality rates between the groups that reach euvolemic status or not for sub-analysis.

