### Study participants and measurements

All patients will be selected from among patients who must be treated with CRRT in four tertiary hospitals in Korea (Seoul National University Bundang Hospital, Seoul National University Hospital, Seoul National University Boramae Medical Center, and Ewha Womans University Mokdong Hospital). Patients aged over 18 years who require CRRT for AKI will be screened for study participation according to the inclusion and exclusion criteria presented in Table 2.

**Table 2 Tab2:** Inclusion and exclusion criteria

Inclusion criteria	
Patients will be eligible for *inclusion* in the study if *all* the following criteria are met:	
1. The treating clinician believes that the patient requires continuous renal replacement therapy for acute kidney injury	
2. The treating clinicians anticipate treating the patient with continuous renal replacement therapy for at least 72 h	
3. Informed consent has been obtained	
4. The patient fulfills one of the following clinical criteria for initiating continuous renal replacement therapy:	
Urine output < 100 mL/6 h that has been unresponsive to fluid resuscitation measures	
K^+^ > 6.5 mmol/L	
pH < 7.2	
Urea > 25 mmol/L	
Clinically significant organ edema in the setting of acute kidney injury	
5. Patients who are over 5% of fluid overload or their total body water/height^2^ ≥ 13 L/m^2^	
Exclusion criteria	
Patients will be *excluded* from the study if, in the opinion or knowledge of the responsible clinician *any* of the following criteria are present:	
1. Patient age is < 18 years	
2. Death is imminent (< 24 h)	
3. There is a strong likelihood that the study treatment will not be continued in accordance with the study protocol.	
4. The patient has been treated with continuous renal replacement therapy or other dialysis previously during the same hospital admission.	
5. The patient has been on maintenance dialysis prior to the current hospitalization.	
6. Any other major illness that, in the investigator’s judgment, will substantially increase the risk associated with the subject’s participation in this study.	

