## Discussion

CRRT is a generally used tool to manage fluid balance among the critically ill patients with AKI when they have medically refractory overhydration [1–4]. Moreover, some recent studies have emphasized the effects of cumulative fluid balance on mortality among CRRT-treated AKI patients [14–16]. However, FO has been mostly quantified as an arithmetical calculation using the following equation: (The sum of daily fluid intake − total output) / (Body weight). This condition has been determined based on the physician’s perception. However, it is not applicable unless a detailed record of fluid monitoring is available, and it cannot differentiate water excess in individual water compartments [17], although such quantification and assessment represents an easy and basic method to evaluate a patient’s fluid status.

InBody S10 (InBody®) is a medical device using MF-BIA and has been approved by the US Food and Drug Administration as an impedance body-fat analyzer that also provides analysis of individual water compartments, such as TBW, ICW, ECW, segmental water values, and ECW ratio (ECW/TBW).

MF-BIA has proven to be useful for assessing volume status in critically ill patients [28, 29] and Rhee et al. [17] showed the effect of MF-BIA-defined volume status on the mortality of critically ill patients with AKI using InBody S20 (InBody®). As there has not yet been a prospective interventional study of fluid balance among CRRT-treated AKI patients using the abovementioned BIA, we will investigate the usefulness of fluid management using the BIA device InBody S10 (InBody®) and compare the results with a generally used quantification method.

To our knowledge, this will be the first multicenter, prospective, randomized controlled trial to assess whether InBody S10-guided volume management is better able to reach a euvolemic status at 7 days after the initiation of CRRT than the quantitation method for volume management is. The endpoint of the VENUS (VolumE maNagement Under body composition monitoring in critically ill patientS on CRRT) study may be of the utmost importance to healthcare providers.

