So far, there is no definite index for determining euvolemic status. Instead, most physicians determine their patients’ volume status based on clinical information, such as intake and output, chest radiographic examination, and physical examination. Therefore, the fluid balance of patients may be managed differently based on the physicians’ opinions, even with the same patients. The abovementioned study by Rhee et al. [17] suggested that TBW/H^2^ and ICW/H^2^ were independently associated with higher in-hospital mortality in male patients with AKI undergoing CRRT, and the group reaching TBW/H^2^ < 13 L/m^2^, which was 13% of total enrolled patients, had a significantly increased level of survival compared to that of other patients. Thus, we will define the euvolemia as the status of TBW/H^2^ < 13 L/m^2^. In addition, our study of fluid removal has revealed that the difference in TBW/H^2^ between CRRT initiation and at day 7 of CRRT,[(BW/H^2^
_at 7days_ – TBW/H^2^
_at CRRT initiation_), especially when it was greater than − 2.1 L/m^2^, was significantly associated with an increased mortality rate, even though it did not reach TBW/H^2^ < 13 L/m^2^ (data not shown). Therefore, we will also consider another measure of euvolemia in this study, namely TBW/H^2^
_at 7days_ – TBW/H^2^
_at CRRT initiation_ < − 2.1 L/m^2^.

There is a chance that patients within the same institution will be correlated more closely than patients at different institutions will. To avoid this issue, we will investigate for the possible clustering of patients at the recruitment institution level and will accommodate such clustering in our models and analysis as required. We have also conservatively calculated the sample size, assuming a high drop-out rate, to overcome this potential problem.

There are a few limitations in this study. First, this study will be investigated in Korean Tertiary Hospitals, which means that the results will require cautious interpretation concerning ethnicity. Second, we have defined euvolemia arbitrarily, although this definition was based on recent data and upon our own study. However, this study is the first study, to the best our knowledge, to determine guidelines for the fluid balance in CRRT-treated critically ill AKI patients using a prospective randomized controlled trial. We expect that the endpoint of the VENUS study will provide the utmost information to healthcare providers.

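### The 5% overload entry floor and the day-7 TBW/H² success thresholds do not match, so near the floor full removal of the overload counts as success or failure according to the patient's body composition.

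*Protocol article*

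**What the plan says.** - **Success at day 7** (Protocol article, Outcome measures). A patient is euvolemic if the change in TBW/H² from D0 to D7 is below −2.1 L/m² or if "TBW/H^2^ at D7 is less than 13 L/m^2". The two limbs are joined by *or*, and one pair of cut-offs serves all patients.
- **Entry** (Study participants and measurements, Table 2, inclusion criterion 5): "Patients who are over 5% of fluid overload or their total body water/height^2^ ≥ 13 L/m^2". These two routes are also joined by *or*.
- **Overload scale** (Discussion). Fluid overload is "The sum of daily fluid intake − total output) / (Body weight".
- **Origin of the cut-offs** (Outcome measures and Discussion). Both come from associations with survival. The value 13 comes from a cited cohort in which the group below it "which was 13% of total enrolled patients". In that cohort TBW/H² was "independently associated with higher in-hospital mortality in male patients with AKI undergoing CRRT". The value −2.1 comes from the investigators' own unpublished data. The Discussion concedes that no definite index of euvolemia exists and that the definition is arbitrary.
- **Analysis** (Statistical analyses). The primary comparison is unadjusted. Adjustment for the baseline value is left to a secondary ANCOVA.

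The article does not relate the 5% entry floor to the 13 and −2.1 thresholds.

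**The concern.** The hypothesis is that guided management reaches euvolemia more often. Entry can be decided on overload as a share of body weight, while success is decided on body water per height squared. The link between the two scales is BMI, which differs between patients. Someone who enters just above the floor and loses exactly the qualifying excess may therefore be scored a failure, while someone who qualified as overloaded may be scored a success without losing any fluid.

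Three things are at stake: what the euvolemia rate means, how sensitive the trial is to a real effect, and the planned mortality comparison between patients who do and do not reach euvolemia. Randomization does not protect that last comparison.

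**Working it through.** **Inputs from the Protocol article:** the overload formula (Discussion); the 5% floor and the TBW/H² ≥ 13 route (Table 2); the success limbs −2.1 and 13 (Outcome measures); 97 evaluable per group, a 19-point difference and power 0.80 (Sample size calculations).

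**Assumptions, not in the documents:** BMI values of 20 to 30 and normal water fractions f of 0.45 to 0.60.

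**1. Linking the scales.** TBW/H² = (TBW/weight) × (weight/H²) = water fraction × BMI. An overload x is x × weight litres. Removing it therefore changes TBW/H² by −x × weight/H² = −x × BMI.

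**2. The −2.1 limb (no water fraction needed).** For full removal to meet it, x × BMI must exceed 2.1.

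| BMI | Fall from full removal of 5% (0.05 × BMI) | Overload that must be removed (2.1/BMI) |
|---|---|---|
| 20 | 1.0 L/m² | 10.5% |
| 24 | 1.2 L/m² | 8.75% |
| 30 | 1.5 L/m² | 7.0% |
| 42 | 2.1 L/m² | 5.0% |

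In litres, at BMI 24 and 1.70 m: weight is 24 × 2.89 = 69.4 kg, and 5% is 3.47 L. The limb needs more than 2.1 × 2.89 = 6.07 L.

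**3. The < 13 limb (depends on f).** After full removal the patient is at f × BMI, and passes only if BMI is below 13/f. That cut is 28.9 at f = 0.45, 26.0 at 0.50, 23.6 at 0.55 and 21.7 at 0.60. For one patient at BMI 24 who enters at 5% and is fully corrected:

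| f | D0 (f × 24 + 1.2) | D7 (f × 24) | Scored |
|---|---|---|---|
| 0.45 | 12.0 | 10.8 | success, but already below 13 at D0 |
| 0.50 | 13.2 | 12.0 | success |
| 0.55 | 14.4 | 13.2 | failure |
| 0.60 | 15.6 | 14.4 | failure |

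**4. The converse.** At normal BMI 22 and f = 0.50, a 5% overload gives D0 TBW/H² = 11.0 + 1.1 = 12.1. The patient enters by the overload route, is below 13 from the start, and is a success at D7 if nothing changes. The lowest row of Table 1 starts at 13, so the tabulated guidance does not cover this patient either.

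**5. Where the mismatch stops.** At 10% overload, full removal meets the −2.1 limb at any BMI above 2.1/0.10 = 21. The problem lies between the 5% floor and 2.1/BMI.

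**6. Possible cost in power (illustration only).** The plan gives no control rate. A rate of 24.5% against 43.5% reproduces a power of 0.80 with 97 per group (pooled-variance formula). Suppose body composition fixed the result in a share s of patients in either arm. The difference would become 19 × (1 − s): 17.1 points at s = 10% and 13.3 points at s = 30%. With the control rate held at 24.5%, power would be about 0.72 and 0.52. The documents do not give s.

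**The case against.** Four arguments on the other side carry weight.

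- **5% is a floor, not the typical patient.** The article gives no distribution of overload at entry, and larger overloads do meet the −2.1 limb when removed. That limb also becomes easier as BMI rises (10.5% at BMI 20, 7.0% at BMI 30), which partly offsets the < 13 limb. This stands. A reader might infer that a larger patient can succeed only by going below normal volume. The arithmetic contradicts that for overloads above 2.1/BMI.
- **Body size alone is not the dividing line.** A reader might infer that only small-bodied patients pass. At f = 0.45 to 0.50 a fully corrected patient passes at any BMI below 28.9 to 26.0. The Assessment of the fluid status section notes that fat holds relatively less water, so f may fall as BMI rises. The determinant is f × BMI, and the documents do not give f.
- **The cut-offs are survival-derived.** They do not claim to mark an individual's normal volume, and the protocol's rationale is that intake-minus-output arithmetic is inadequate. This is a fair reason to keep the endpoint. It does not remove the need to say what the endpoint means, and calling the definition arbitrary does not disclose the mismatch with the entry rule.
- **Randomization balances body build.** The same rule applies to both arms under 1:1 allocation. A reader might infer a biased treatment comparison, but the documents do not support that. The argument does not extend to mortality by euvolemia status, because that comparison is not randomized.

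**Conclusion.** The point holds as a mismatch of scales near the entry floor. From the protocol's own formula, full removal of a 5% overload cannot meet the −2.1 limb unless BMI exceeds 42. At BMI 20, 24 and 30 the overload removed must exceed 10.5%, 8.75% and 7.0% of weight. These figures need no outside value. Which of these patients pass the < 13 limb depends on an assumed water fraction. How many patients are affected, in either direction, cannot be derived from the article.

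The consequences are misclassification, lower sensitivity, a euvolemia rate that cannot be read as the share of patients whose overload was removed, and confounding of the mortality comparison by body build. The loss of power is real in direction, but its size is only illustrated above.

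**What to change.** Keep the primary endpoint and change the analysis around it.

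1. **Primary analysis.** Fit a model for the binary endpoint with arm and D0 TBW/H², in place of leaving baseline adjustment to a secondary ANCOVA. Report the adjusted risk difference so that it can be compared with the planned 19 points. D0 BMI may be added, but D0 TBW/H² already contains the build term.
2. **Supportive analysis.** Pre-specify the same comparison in patients with D0 TBW/H² ≥ 13, which removes those who already met the absolute limb at entry.
3. **Reporting.** Show success by arm within groups of D0 TBW/H² and of D0 BMI.
4. **Mortality by euvolemia status.** Adjust for the same baseline values and describe it as a non-randomized comparison.
5. **Interpretation.** State that success means reaching a survival-derived TBW/H² threshold, not full removal of the qualifying overload.
6. **Consistency.** The sponsor should reconcile inclusion criterion 5 with the outcome thresholds. No threshold is proposed here.

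The cost is analysis-plan wording and a few extra tables. D0 TBW/H² is measured in both arms, and entry weight is needed for the overload calculation. The downside is that some reported rates, particularly in the D0 ≥ 13 group, may look less favourable.

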### Assessment of the fluid status

For participants in the control group, clinical information obtained by the physician is the standard of judgment. However, the participants will be measured by InBody S10 (InBody®) at D0 and D7, and the results will be recorded. Clinical information will be composed of four items: body weight in the morning; hemodynamic stability; absence of symptoms and signs of hypervolemia (dyspnea, edema, and crackle) or hypovolemia (dizziness and orthostatic hypotension); and daily intake and output. For participants in the treatment group, InBody S10 (InBody®) will also be measured at 9:00 a.m. on D0, D1, D2, and D7. Table 1 shows the guideline of fluid management for the treatment group. However, both the physicians and participants will be blinded to the results of InBody S10 (InBody®) analysis.

InBody S10 (InBody®) is a medical device that has been approved by the US Food and Drug Administration as an impedance body-fat analyzer. The device provides the following parameters: TBW, ICW, ECW, segmental water values, ECW ratio (ECW/TBW), FFM, soft lean mass (SLM), segmental lean mass, body fat mass (BFM), percentage body fat (PBF), and TBW/FFM.

The BIA method calculates body composition using the resistance value (impedance) that appears due to the difference in electrical conductivity according to the biological characteristics of each tissue. Electrical conductivity is proportional to the amount of water and electrolytes, and the water content of fat tissue is relatively smaller than that of other tissues, which leads to a decrease in electrical conductivity when the fat content increases. Among the components of the body, body water is the component that passes an electrical current, so the volume of water in the body can be obtained by measuring the resistance value obtained from body water [21].

### Clinical and laboratory evaluations

Physical examination, comorbidity and medication will be reviewed. Laboratory evaluations, including complete blood cell counts (CBC), electrolytes, creatinine, protein, albumin, calcium, phosphorous, total cholesterol, triglyceride, low-density lipoprotein cholesterol, high-sensitivity C-reactive protein (hs-CRP), and *N*-terminal prohormone of brain natriuretic peptide (NT-proBNP) will also be performed in the morning in the intensive care unit.

### Safety issues

The InBody S10 (InBody®) method approved by the US Food and Drug Administration has been used in clinical practice. Applying weak alternating currents into the body is known to not be harmful.

### Sample size calculations

No previous report has evaluated the effect of InBody S10 (InBody®)-guided fluid management on CRRT-treated patients. We will randomly divide the enrolled participants equally into two groups. Assuming a 19% difference in the rate of achieving euvolemic status between the two groups with 0.8 of power, two-sided, and 0.05 of alpha, 97 participants will be allocated in each group. However, 122 participants will be required to enroll in each group due to a 20% withdrawal rate.

### Statistical analyses

The statistical analyses will be conducted both on a per-protocol (PP) and an intention-to treat (ITT) basis. For PP analysis, all participants who complete the study will be included to evaluate the primary and secondary outcomes. For the ITT analysis, all participants who are enrolled and randomized to one of the two groups and who complete the first visit will be included. Basic statistics will be reported in terms of the mean ± SD for continuous variables, or as percentages for categorical variables. Differences between groups will be analyzed using Student’s *t* test for continuous variables and the *χ*^2^ test or Fisher’s exact test for categorical variables. The primary outcome will be compared with Student’s *t* test. An analysis of covariance (ANCOVA) will be used to analyze the primary outcome as the secondary analysis to adjust the baseline value. Multivariate Cox proportional hazard regression models will be used to analyze the time to mortality. Although the institutions are mainly located in large cities, thereby limiting the likelihood of any important cluster effect, we will be sure to accommodate possible clustering in our models and analysis as required. A value of *P* < 0.05 will be considered statistically significant. All analyses will be performed using SPSS Statistics software (v21.0; IBM Corporation, Armonk, NY, USA).

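### The primary outcome is a yes/no rate, but the plan tests it with Student's t test and ANCOVA against its own rule for categorical variables, and covers institution, the stratification factor, only conditionally

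*Protocol article*

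**What the plan says.** - **Endpoint** (Outcome measures): "The primary outcome is to compare the rate of euvolemic status at 7 days from the CRRT start". A patient counts as euvolemic when the change in TBW/H² from D0 to D7 "is less than − 2.1 or TBW/H^2^ at D7 is less than 13 L/m^2". Each patient is therefore a yes or a no.
- **Sample size** (Sample size calculations): "Assuming a 19% difference in the rate of achieving euvolemic status between the two groups", with 80% power and two-sided alpha 0.05, gives 97 per group, raised to 122 for 20% withdrawal.
- **General rule for tests** (Statistical analyses): the t test for continuous variables, and the χ² "test or Fisher’s exact test for categorical variables".
- **Primary test** (the next sentence): "The primary outcome will be compared with Student’s *t* test".
- **Secondary analysis of the same outcome**: "An analysis of covariance (ANCOVA) will be used to analyze the primary outcome as the secondary analysis to adjust the baseline value".
- **Institution**: "Randomization will be stratified based on the institution and will utilize a randomized block design" (Randomization). Statistical analyses and Discussion both say that possible clustering by institution will be accommodated as required. Neither names a method or says what would trigger it.

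**The concern.** The endpoint and the sample size concern a proportion. The named test and the named covariate-adjusted analysis belong to a continuous measurement. The baseline adjustment strengthens that reading: the change limb of the euvolemia rule has no value at D0, so euvolemic status has no matching baseline, whereas TBW/H² does. An analyst could reasonably compare mean D7 TBW/H², compare mean change, or apply a t test to 0/1 data, and could defend each from the text.

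This decides which result carries the single P < 0.05 threshold. The trial is open-label, so the choice should not remain open until data are in hand. Institution is a second, smaller open choice. It is built into the allocation, but it enters the analysis only if someone later judges it to be required.

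**Working it through.** **1. The plan's own figure.** Withdrawal: 97 / (1 − 0.20) = 121.25, rounded up to 122 per group and 244 in total. This reproduces. The 97 cannot be derived from the stated inputs alone, because no control rate is given. It does fit a comparison of proportions. For example, with assumed rates of 27% and 46% and the unpooled formula:

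n = (1.960 + 0.842)² × (0.27×0.73 + 0.46×0.54) / 0.19² = 7.849 × 0.4455 / 0.0361 = 96.9, rounded up to 97.

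Over all control rates, the pooled formula for a 19-point difference peaks at 108 per group (43% against 62%). The sizing is thus consistent with a test of rates and is not shown to be wrong.

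**2. Does the t test itself mislead on 0/1 data?** With N = 194, the uncorrected χ² statistic equals N·t² / (t² + N − 2). At the t cut-off of 1.9724 (192 df), t² = 3.890 and χ² = 194 × 3.890 / 195.890 = 3.853, against the usual 3.841. Enumerating all 98 × 98 = 9,604 possible tables at 97 per arm, the two tests never disagree at 0.05. Type I error is 0.049 to 0.052 for both at the rates tried, and power at 27% against 46% is 0.790 for both.

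**3. Rate or mean: does the choice matter?** The documents give no distribution for TBW/H², so these inputs are assumptions: D0 mean 16 or 17 with SD 2, values below 13 set to 13; control change mean −1 with SD 1.5, 2 or 3; the plan's two-limb euvolemia rule; 97 per arm; 10,000 simulated trials per setting.
- With a true 19-point difference, χ² on the rate and a t test on mean D7 TBW/H² gave different verdicts at 0.05 in about 18% to 30% of trials.
- With no true difference, claiming success if either was significant gave a type I error of about 8% to 9%. Allowing mean change as a third option gave about 10% to 12%.

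**4. Leaving out institution.** Assume four equal sites with 24 per arm each and control rates of 20, 30, 50 and 60%.
- Variance used by the unstratified test under no effect: 0.40 × 0.60 = 0.240.
- Average within-site variance: (0.16 + 0.21 + 0.25 + 0.24) / 4 = 0.215.
- The standard error is therefore too large by √(0.240 / 0.215) = 1.057, about 6%.

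Simulation (40,000 trials per setting), unstratified test against Cochran–Mantel–Haenszel (CMH):

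| Assumed site rates (%) | Type I, unstratified | Type I, CMH | Power at +19 points, unstratified | Power, CMH |
|---|---|---|---|---|
| 40/40/40/40 | 0.048 | 0.048 | 0.76 | 0.76 |
| 30/35/45/50 | 0.047 | 0.050 | 0.76 | 0.76 |
| 20/30/50/60 | 0.036 | 0.049 | 0.77 | 0.80 |
| 10/30/50/70 | 0.027 | 0.051 | 0.78 | 0.84 |

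The t test and χ² figures agree to four decimals in every row, so one unstratified column serves for both.

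**The case against.** The strongest defence is that the t test, applied literally to the stated rate, changes no decision, as step 2 shows. The endpoint wording is clear, and a reasonable statistician would repair the slip by using the χ² rule that the paragraph already supplies. The first part stands, so the t test cannot be said to inflate error or lose power on 0/1 data. The second does not rescue the text. The primary test is named explicitly, directly after the rule that it breaks, and the baseline-adjusted ANCOVA points towards a mean. An unseen analysis plan does not cure a contradiction stated here.

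A reader might also infer two stronger points that the document does not support.
- **That the plan ignores institution.** It does not: two sections promise to accommodate institution-level clustering. The fair criticism is that the promise is conditional and the named primary test has no institution term. A condensed article may also leave the method to a fuller document.
- **That covariate adjustment would recover substantial power.** At assumed rates of 27% and 46% with moderate site differences, the t test has power of about 0.79 and a logistic model with institution about 0.81. Adding a baseline covariate gives 0.81, 0.82 or 0.87 as its assumed log-odds slope per SD goes from 0 to 0.5 to 1. Nearly all the gain comes from a slope that the document does not give. The two-limb rule also makes a simple D0 slope doubtful: a low D0 helps the absolute limb, and a high D0 leaves more room for the change limb.

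**Conclusion.** The contradiction is real and lies in the confirmatory analysis: a rate is defined and sized, while methods for a mean are named for it. Its main consequence is that the primary quantity is not fixed. Under the assumed distributions in step 3, the choice changes the significance verdict in about a fifth to three tenths of trials, and free choice between the two raises a 5% error rate to about 8% to 9%. Those figures illustrate the room left open. They do not predict what the investigators would do.

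The institution point is secondary. The loss is nil if sites are alike, about 3 points of power at assumed site rates of 20/30/50/60%, and larger only if sites differ more. The unstratified test errs on the conservative side. Nothing here shows that 97 or 122 per group is wrong.

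**What to change.** In Statistical analyses, replace the t test sentence with one primary analysis: the D7 euvolemia rate compared between arms, either by a Cochran–Mantel–Haenszel test stratified by institution or by logistic regression with institution as a term. Choose one in advance and report the risk difference with its 95% CI. State that institution is always included, in place of the conditional wording for this outcome. Adjustment for D0 TBW/H² is optional and, if wanted, should be declared now.

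Reword the ANCOVA sentence so that it applies to continuous D7 TBW/H² adjusted for D0, as a named secondary analysis. Any t test of TBW/H² belongs there too.

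The cost is two or three sentences, made before any outcome data are analysed. Institution and TBW/H² at D0 and D7 are already recorded in both arms, and the sample size stays at 122 per group.
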